## Abstract

**Background:**

Being diagnosed with cancer causes major psychological distress, yet the majority of newly diagnosed cancer patients lack psychological support. Internet interventions overcome many barriers for seeking face-to-face support and allow for independence in time and place. We assess efficacy and feasibility of the first web-based stress management intervention (STREAM: STREss-Aktiv-Mindern) for newly diagnosed, German-speaking cancer patients.

**Methods/design:**

In a prospective, wait-list controlled trial 120 newly diagnosed cancer patients will be included within 12 weeks of starting anti-cancer treatment and randomized between an immediate (intervention group) or delayed (control group) 8-week, web-based intervention. The intervention consists of eight modules with weekly written feedback by a psychologist (“minimal-contact”) based on well-established stress management manuals including downloadable audio-files and exercises. The aim of this study is to evaluate efficacy in terms of improvement in quality of life (FACT-F), as well as decrease in anxiety and depression (HADS), as compared to patients in the wait-list control group. A sample size of 120 patients allows demonstrating a clinically relevant difference of nine points in the FACT score after the intervention (T2) with a two-sided alpha of 0.05 and 80 % power. As this is the first online stress management intervention for German-speaking cancer patients, more descriptive outcomes are equally important to further refine the group of patients with the largest potential for benefit who then will be targeted more specifically in future trials. These descriptive endpoints include: patients’ characteristics (type of cancer, type of treatment, socio-demographic factors), dropout rate and dropout reasons, adherence and satisfaction with the program.

**Discussion:**

New technologies open new opportunities: minimal-contact psychological interventions are becoming standard of care in several psychological disorders, where their efficacy is often comparable to face-to-face interventions. With our study we open this field to the population of newly diagnosed cancer patients. We will not only assess clinical efficacy but also further refine the target population who has the most potential to benefit. An internet-based minimal-contact stress management program might be an attractive, time- and cost-effective way to effectively deliver psychological support to newly diagnosed cancer patients and an opportunity to include those who currently are not reached by conventional support.

**Trial registration:**

ClinicalTrials.gov NCT02289014.

## Background

### Impact of cancer on mental health

Every second cancer patient suffers from clinically relevant psychosocial distress [1]. Psychosocial distress encompasses emotional lability, rearranging of roles and responsibilities, changing of future plans, fear of recurrence, depression and anxiety and is associated with decreased quality of life [2–4]. In addition, high levels of distress lead to reduced compliance with treatment and more side effects [5, 6]. Conversely, side effects of cancer treatment like fatigue, nausea and pain may trigger distress and, therefore, impact psychological adjustment.

### Efficacy of psycho-oncological interventions and Utilization of psycho-oncological support

Cognitive behavioural techniques, including relaxation techniques [7] and mindfulness based stress reduction [8], significantly reduce distress, depression and fatigue and increase quality of life in cancer patients, albeit effect sizes in randomized controlled trials are small to medium [9]. Moreover, psycho-oncological interventions may reduce side effects of cancer treatment [7, 9–13]. Yet many patients do not seek or have access to psycho-oncological support, even when high levels of distress are experienced [14]. This seems especially true for male patients [15, 16] and patients with cancer other than female breast cancer [15].

### Web-based interventions in psycho-oncology

The internet has the potential to reach patients and to overcome barriers towards using psycho-oncologic support (e.g. stigma and privacy concerns, geographical distance form providers, time constraints to adhere to additional appointments during office hours) [17]. The vast majority of cancer patients already uses the internet as a source of information [18]. Furthermore, from the providers’ perspective, internet interventions are time- and cost-effective, and thus are of special interest for the health care system. Scientific interest in internet interventions for non-cancer patients has grown rapidly over the last decade. Efficacy of this novel treatment format has been demonstrated for a variety of mental disorders in a substantial number of randomized controlled trials (RCTs). Reviews and meta-analyses show moderate to large effects, post-treatment [19–22]. Studies directly comparing internet interventions with face-to-face therapy report similar outcomes across various mental disorders (e.g. anxiety disorders, depression) and health concerns associated with bodily symptoms (e.g. tinnitus, sexual dysfunction) [23]. There are also a few long-term follow-up studies showing lasting effects over as much as five years post-treatment [24]. Data on web-based interventions for cancer patients are scarce [25, 26]. There is no cancer-specific stress management program for cancer patients in German. Also, little is known on the characteristics (including age, sex, education, type of cancer) of patients who participate and benefit from a web-based intervention.

### Objective and research questions

In a prospective randomized wait-list controlled trial we assess the efficacy of a minimal-contact online intervention in newly diagnosed cancer patients. More specifically, we assess whether patients who undergo the online intervention report a better quality of life (FACIT-F), are less anxious and depressive (HADS-D), less stressed (DT), and cope better with their disease (FAH II) as compared to patients in the wait-list control group. This is the first online stress management intervention in German for cancer patients (STREAM: **STRE**ss **A**ktiv **M**indern). Moreover, since it is novel to recruit patients via the internet rather than face-to-face, we set out to determine patients characteristics for participation and benefit. These descriptive outcomes include: patients’ characteristics (type of cancer, type of treatment, sociodemographic factors), patients’ adherence as well as satisfaction with the program.

## Methods/design

In a prospective randomized controlled intervention study (Fig. 1) patients are randomized 1:1 (mixed randomization scheme using unequal block randomization) between the intervention group and the wait-list control group. Patients are stratified according to baseline stress level (distress thermometer ≥ *vs* < 5 [27]). A total of 120 newly diagnosed adult (>18 years) cancer patients who started first-line treatment (either systemic treatment - including chemotherapy, hormonal treatment or targeted therapy - or radiotherapy) no longer than 12 weeks earlier are included after giving informed consent. Patients who undergo treatment for a first relapse of a tumor previously treated with curative intent are also eligible. Patients are required to read and write in German, have internet-access as well as basic computer skills.

**Fig. 1 Fig1:**
[figure not shown]
Study design

Patients are recruited via the public website of STREAM [28]. We adopt an *active* recruitment strategy in the German speaking countries Switzerland, Germany, and Austria via the following channels: a) Links to the public website of STREAM on health related websites, such as Cancer Leagues, Cancer Hospitals, Patient advocate websites b) distribution of flyers in hospitals and during cancer conferences, c) active communication to the media d) advertisement via Google Ad and Facebook Ad. The Northwest and Central Swiss Ethics Committee has approved the study (EKNZ 339/13).

### Intervention

We developed the web-based intervention STREAM based on well-described and established stress management interventions manuals [29–33], which we adapted to the web-context. The program aims at improving intra- and interpersonal coping strategies, reducing perceived stress and anxiety as well as enhancing quality of life. We assessed the usability of the program in the target population of cancer patients in a previous study ([name], et al. Usability evaluation of the web-based stress management program STREAM for newly diagnosed cancer patients. submitted. 2016).

STREAM consists of eight modules (Table 1) which can be completed in 60 to 90 min each. Participants are asked to work through one module per week, i.e. the intervention takes 8 weeks in total. Every module starts with a short mindfulness breathing exercise and includes (a) text-based psycho-education, (b) reflection on the current individual emotional status and (c) acquisition of strategies including several exercises. Within each module exercises on relaxation techniques and guided-imagery exercises are available as audio files and can be downloaded to various devices (e.g. PC/Mac, tablets, smart phones, MP3 Players). Patients are encouraged to use the audio files daily. Participants receive weekly feedback and individual support by a psychologist from the study team via secure integrated e-mail (=”minimal-contact”). Patients can use the secure chat function to contact the psychologist.

**Table 1 Tab1:** Content of the web-based stress management program STREAM

Module		Psychoeducation	Reflection on status	Strategies
1.	Introduction: What is stress?	Nature of stress in general and in specific cancer-related situations	My individual stressors	Diary^b^
			Stress protocol	Body scan^a^
				Stress protocol ^b^
2.	Body stress reduction	Bodily sensations during stress and side effects of anticancer treatment	Relaxation protocol	Progressive muscle relaxation ^a^
				Beach promenade^a^
				Relaxation protocol^b^
3.	Cognitive stress reduction	Thoughts and their interaction with emotions and bodily sensations	My negative thought patterns	Negative thought cycle^a^
				Relationship of body position and thoughts^b^
				Thinking styles and reflection^b^
				Thoughts on clouds^a^
4.	Emotional stress reduction	Feelings and cancer-related emotions as anxiety and worries were explained	My feelings and worries	Mountain meditation^a^
				Emotional emergency kit^a^
5.	Mindfulness and acceptance of thoughts and emotions	Meaning of mindfulness and acceptance and their implementation in daily life in contrast to the active strategies learned in modules 1–4	My definition and experiences with acceptance	Acceptance story ^a,b^
				Body scan^a,b^
				Integration of mindfulness^b^
				Winter walk^a^
				Spring awakening^a^
6.	Activation of resources: quality of life and pleasure	Introduction of models of the balance between burden and resources	My individual resources	Health-cycle ^b^
				Planning activities^b^
				Week planner ^b^
				Friendly feelings with our own body^a^
				Enjoyment training^b^
7.	Activation of resources: social network and communication skills	Social network and the role of a supportive environment	My individual social network and current needs	Communication skills^b^
				Beach promenade^a^
				Winter promenade^a^
				Spring awakening^a^
8.	Summary	Concluding an overview and documentation of the last 7 weeks	My experiences with the program	Four seasons^a^

^a^Audio file: story, relaxation or guided imaginary exercise, ^b^Instructions and worksheets

### Assessments

Assessments are summarized in Table 2 and are conducted via an open source survey application [34] at baseline (T1), after the 8-week intervention or wait (control group), respectively (T2), as well as after an additional 8 weeks (T3, follow-up for the intervention group or after the delayed intervention for the wait-list group, respectively (Fig. 1)).

**Table 2 Tab2:** Schedule of assessment

Instrument	T1		T2	T3
	Baseline	Weekly during intervention	Post intervention	Follow up
Socio-demographics	x			
Medical history	x		x	x
Distress Thermometer (DT)	x	x	x	x
Functional Assessment of Chronic Illness Therapy-Fatigue (FACT-F)	x		x	x
Hospital anxiety and depression scale (HADS)	x		x	x
Suicidal tendency (Suicid Item Beck Depression Inventory BDI)	x		x	x
Acceptance and Action Questionnaire (AAQ)	x		x	x
Working Alliance Inventory (WAI-SR)		x		
System Usability Scale (SUS)		x^a^		
Client Satisfaction Questionnaire (CSQ-8)			x^b^	x^b^

^a^ Assessed twice (after the first and last module); ^b^ Assessed post-intervention: for intervention group to T2, for control group to T3

**Socio-demographic** information is self-reported and includes age, gender, marital status and partnership, children, education, monthly household income and employment status.

**Medical history** includes information regarding tumor diagnosis, time since diagnosis, past and current cancer treatments (curative or palliative setting), past and current psychosocial support and psychopharmacological medication and is obtained from both patients and their treating physicians.

### Efficacy outcomes

The main efficacy outcome is quality of life (FACT) including assessment of fatigue (FACT-F) [35] at T2. We use the validated German Version **functional assessment of chronic illness therapy-fatigue (FACIT-F)** which is freely available from the website www.facit.org.

To assess anxiety/depression and psychological distress the ** hospital anxiety and depression scale (HADS)** [36] and the **distress thermometer (DT)** in the German version [27] are used, respectively. Patients are stratified based on their level of baseline distress. A score of five or higher at the DT visual analogue scale is a cut-off score for a clinically significant level of distress [27]. To longitudinally describe psychological coping with cancer we use ‘the acceptance and action questionnaire (AAQ)’ in its German version ‘***Fragebogen zur Akzeptanz und Handeln***
**(FAH II)’** [37], which we adapted specifically for cancer patients with three additional items concerning their coping with the disease.

The online support program STREAM is not designed to support suicidal patients in acute crises. For safety reasons, **suicidal tendency** is assessed by the single suicide item out of the Beck Depression Inventory (BDI) [38]. Patients with a score higher than one are contacted by telephone to reassess suicidal ideation and, if needed, patients are instructed to call for local psychiatric support.

### Evaluation of the intervention

To evaluate the therapeutic alliance between patient and therapist ﻿the ** short version of the working alliance inventory (WAI-SR)** with subscales for bond, tasks and goals is used in its German version [39] weekly after each module. Usability and user satisfaction is assessed with the **system usability scale (SUS)** [40] and the Client Satisfaction Questionnaire (CSQ-8; in its German version: *Fragebogen zur Messung der Patientenzufriedenheit* ZUF-8; [41]. Satisfaction with the online therapeutic contact will be assessed with predefined questions described by Knaevelsrud and Maerker [42]. In addition, after each module, patients’ satisfaction with the module is assessed with an open question. Data on adherence (frequency and duration of logins, website activity, using/downloading different exercises, and the number of modules completed) are collected via the backend functions of the online program STREAM.

### Statistical analyses and sample size calculation

Based on previous studies [43] including recent data on cancer patients [44], a difference of nine points in the FACT score is both, clinically significant and realistic. In order to demonstrate a 9-point difference between baseline and T2 (after 8 weeks) in the intervention group with a statistical power of 0.80 at a significance level of 0.05 (two-sided), 60 participants are needed in each of the two conditions. We assume normally distributed data in both groups with a standard deviation of ±18 [45]. Data preparation of all continuous dependent variables will include tests for normality, homogeneity of variances, and examination of outliers. If not normally distributed, variables will be subjected to adequate transformation. Intent-to-treat samples will be used to analyze data. The choice of statistical approach depends on the amount of missing data at T2 and T3. If less than 12 % of data are missing, the Last Observation Carried Forward (LOCF) method will be applied to estimate effects. Then, the outcome will be computed with an analysis of covariance (ANCOVA), using the pre-scores as a covariate and the post-scores as the dependent variable. If more than 12 % of data are missing, we will use linear mixed models. This method is recommended for intent-to-treat-analyses with a high amount of dropouts due to its potential to reduce bias caused by missing data. Regression analyses will be used to identify predictors of treatment outcome.

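### The sample-size sentence powers a within-arm change from baseline, contradicting the between-arm comparison planned; 60 per condition at 80% power follows from neither reading

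*Protocol article*

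**What the plan says.** The section on statistical analyses and sample size calculation first states that "a difference of nine points in the FACT score is both, clinically significant and realistic". It then sizes the trial to show a "9-point difference between baseline and T2 (after 8 weeks) in the intervention group", with power 0.80 and two-sided alpha 0.05, and concludes that "60 participants are needed in each of the two conditions". On variability it says: "We assume normally distributed data in both groups with a standard deviation of ±18". It does not say whether 18 is the SD of the score or of the change.

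The rest of the article concerns a comparison of arms. The abstract describes the same 120 patients as enough for a "clinically relevant difference of nine points in the FACT score after the intervention (T2"), with no reference to baseline or to a single arm. The objective asks whether treated patients do better "as compared to patients in the wait-list control group". The efficacy outcomes section names FACT at T2 as the main outcome. The planned ANCOVA is fitted "using the pre-scores as a covariate and the post-scores as the dependent variable".

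**The concern.** A change from baseline inside the intervention arm and a difference between arms at T2 are different quantities. They coincide only if the wait-list arm stays, on average, where it started. The article therefore gives two hypotheses for the same 120 patients, and the one in the methods section is not the one the analysis tests.

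Two things are at stake. A reader cannot tell which effect the 80% power belongs to, because the number does not match the sentence that introduces it. And if the nine points really were an expected gain in treated patients alone, the effect tested would be nine points minus whatever happens in controls, and the power for it could be well above or well below 80%.

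**Working it through.** **Inputs, all from the sample-size section.** Difference 9, SD 18, so standardised effect 9/18 = 0.5; two-sided alpha 0.05 (z = 1.960); power 0.80 (z = 0.842); stated n = 60 per condition.

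**1. The hypothesis as worded (within-arm).**
- If 18 is the SD of change: n = ((1.960 + 0.842) × 18/9)² = 31.4, so 32 by normal approximation. The paired t-test gives 33.4, so 34. Sixty patients would give 97% power, and no second arm enters the calculation.
- If 18 is the SD of the score at each visit, the SD of change is 18 × √(2(1 − ρ)), where ρ is the baseline-T2 correlation. The article gives no ρ, so a range is assumed (paired t-test):

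| Assumed ρ | SD of change | n |
|---|---|---|
| 0 | 25.5 | 65 |
| 0.3 | 21.3 | 46 |
| 0.5 | 18.0 | 34 |
| 0.7 | 13.9 | 21 |

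To obtain 60, the SD of change would have to be about 24.5, meaning that a patient's two scores are almost uncorrelated.

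**2. The between-arm hypothesis, unadjusted.**
- n per arm = 2 × (1.960 + 0.842)² × (18/9)² = 62.8, so 63. The t-test gives 63.8, so 64.
- Power at 60 per arm: Φ(0.5 × √30 − 1.960) = Φ(0.779) = 0.782. By t-test it is 0.775.
- The result is the same if 18 is the SD of change and the arms are compared on change.

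So 60 is near the two-sample answer but does not quite reach 80%.

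**3. The between-arm hypothesis under the planned ANCOVA.** Taking 18 as the score SD, the residual SD is 18 × √(1 − ρ²). Power at 60 per arm for a true nine-point difference (t-test on the residual SD):

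| Assumed ρ | Residual SD | Power |
|---|---|---|
| 0 | 18.0 | 0.78 |
| 0.25 | 17.4 | 0.80 |
| 0.5 | 15.6 | 0.88 |
| 0.7 | 12.9 | 0.97 |

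**4. If the nine points were a within-arm gain.** The between-arm effect is then 9 minus the control arm's change. Unadjusted t-test power at 60 per arm, SD 18, with assumed control changes:

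| Assumed control change | Between-arm effect | Power |
|---|---|---|
| −3 | 12 | 95% |
| 0 | 9 | 78% |
| +2 | 7 | 56% |
| +3 | 6 | 44% |
| +4 | 5 | 33% |

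ANCOVA at an assumed ρ of 0.5 raises the +2, +3 and +4 rows to 68%, 55% and 41%. None of the control changes comes from the article.

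**The case against.** The strongest reply is that this is a slip of wording and not a faulty design. The sentence asks for patients in both conditions and the next gives an SD for both groups; a within-arm test needs neither. The abstract gives the same patients, points, alpha and power as a difference at T2. The two-sample answer, 63 to 64, is much closer to 60 than 34 is. This largely stands, and it is the most likely explanation. It does not remove the contradiction, and 60 at 80% is still not exact without adjustment.

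A reader might go further and infer three things that the article does not support:

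- That the trial could claim efficacy from an uncontrolled pre-post change. The aim, the main outcome and the ANCOVA are all about the arms at T2, and nothing in the article permits a within-arm efficacy claim.
- That the 80% power has nothing to do with the randomised comparison. For a nine-point between-arm difference, 60 per arm gives about 78% unadjusted, and the planned ANCOVA reaches 80% at a modest correlation.
- That power is really about 44%. This needs both a within-arm origin for the nine points and a control gain of exactly three points. The article establishes neither. Patients enter within 12 weeks of starting anti-cancer treatment, so controls could worsen as well as improve.

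**Conclusion.** The sizing hypothesis is wrong as written. It names a contrast that the trial does not test and conflicts with the abstract, the objective and the ANCOVA. The stated 60 per condition at 80% power follows from no natural reading: within-arm gives 34 if 18 is the SD of change (65 down to 21 if it is the score SD with ρ assumed between 0 and 0.7), and between-arm gives 64.

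On the likely reading, a misdescribed two-sample calculation, the practical size is small: about 78% power instead of 80% before adjustment, recovered by ANCOVA at ρ of about 0.25 or more if 18 is the score SD. The larger loss of power arises only if the nine points came from within-arm data. That depends on the cited sources, so it stays an open question for the sponsor. The point is an inconsistency to reconcile, and not evidence that the design or the analysis is unsound.

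**What to change.** In the sample-size section:

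- Restate the target as a nine-point difference between the intervention and wait-list arms in mean FACT score at T2, adjusted for baseline.
- Say whether 18 is the SD of the T2 score or of the change.
- Confirm that the nine points is a between-group difference in the sources cited. If it is not, give the control-arm change that was assumed and the power that results.
- Restate the power at 60 per arm as about 78% unadjusted, or as 80% or more under ANCOVA with a stated baseline-T2 correlation of at least about 0.25 (with 18 as the score SD). Rewording the hypothesis alone would leave 60 and 0.80 unreconciled.

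The cost is a few sentences. Enrolment, randomisation and analysis stay as they are. The one downside is a slightly less favourable power figure if no correlation is stated. The article reports 80 of 120 patients recruited, so this can be settled before analysis.

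### On its printed inputs, 60 patients per arm gives about 78 % power rather than 80 %, and no allowance for dropout is visible

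*Protocol article*

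**What the plan says.** The section on statistical analyses and sample size calculation gives all the inputs. It holds that "a difference of nine points in the FACT score is both, clinically significant and realistic", sets the calculation "with a statistical power of 0.80" and a two-sided significance level of 0.05, and adds: "We assume normally distributed data in both groups with a standard deviation of" ±18. From these it concludes that "60 participants are needed in each of the two conditions". The difference to be shown is worded there as a "9-point difference between baseline and T2 (after 8 weeks) in the intervention group".

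The abstract (Methods/design) repeats the claim: "A sample size of 120 patients allows demonstrating a clinically relevant difference of nine points in the FACT score" at T2, again with 80 % power and two-sided alpha 0.05. There it follows directly on an aim framed as a comparison with the wait-list control group. The main Methods/design section gives 1:1 randomisation and 120 patients included in total.

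On missing data, the abstract lists the dropout rate and its reasons as descriptive endpoints. The statistical section plans LOCF with ANCOVA on the baseline score if less than 12 % of data are missing, and linear mixed models if more are. No expected dropout rate and no correlation between baseline and T2 scores is stated.

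**The concern.** A reader who puts the printed inputs into the standard two-sample formula does not get 60. The number included equals the number said to be needed, so any patient without a T2 assessment takes the trial further below the stated power. The abstract presents 80 % power for nine points as a property of the trial, and a null result would be read against that figure. If it is too high, such a result would count as stronger evidence against a 9-point benefit than it is.

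**Working it through.** **Inputs.** Difference 9, SD 18 in both groups, two-sided alpha 0.05, power 0.80 (statistical section); 1:1 allocation and 120 patients (Methods/design). Standardised difference: 9/18 = 0.50.

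**Attempt to reproduce 60 per arm.**

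- Normal approximation: n = 2 × (1.960 + 0.842)² × (18/9)² = 2 × 7.849 × 4 = 62.8, so 63 per arm (126 in total).
- Two-sample t-test (noncentral t): 63.8, so 64 per arm (128 in total).
- One-sided test, normal approximation: 50 per arm.
- Literal within-group reading, paired t-test, with 18 taken as the SD of the change: 33.4, so 34 patients in one group.

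None of these gives 60.

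**Power at 60 per arm, complete data.** Normal: the expected z is 0.50 × √(60/2) = 2.739, and Φ(2.739 − 1.960) = Φ(0.779) = 78.2 %. The t-test gives 77.5 %.

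**If outcomes are missing.** The article gives no rate. The 12 % below borrows its threshold for switching methods, and 20 % is an assumption for illustration. Reducing n approximates the loss of information. At 12 %, 60 × 0.88 = 52.8, about 53 per arm.

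| Missing | n per arm | Unadjusted power, normal | Unadjusted power, t |
|---|---|---|---|
| 0 % | 60 | 78.2 % | 77.5 % |
| 12 % (assumed) | 53 | 73 % | 72 % |
| 20 % (assumed) | 48 | 68.8 % | 67.9 % |

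**What the planned baseline adjustment could add.** Suppose 18 is the SD of the T2 score and r is its correlation with baseline. ANCOVA then reduces the SD to 18 × √(1 − r²). Against the t-test requirement of 63.77 per arm, 80 % power needs r = √(1 − n/63.77):

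- n = 60: √(1 − 0.941) = 0.24
- n = 53: √(1 − 0.831) = 0.41
- n = 48: √(1 − 0.753) = 0.50

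With an assumed r = 0.5, the SD becomes 18 × √0.75 = 15.6. Power (t) is then 88 % with complete data, 84 % at 12 % missing and 80 % at 20 % missing.

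**The case against.** The strongest reply is that the shortfall is trivial and the calculation conservative. Three or four patients per arm is about 2 points of power. By the t-test, 60 per arm has 80 % power for about 9.28 points instead of 9, or for 9 points with an SD of about 17.45 instead of 18, and no planning SD is known that precisely. The analysis will be baseline-adjusted, so a correlation of about 0.24 is enough with complete data. Sizing a trial without the covariate is common, and a condensed article need not print a correlation.

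Much of this stands. A reader might infer that the trial is underpowered. The document does not support that, because the power of the planned analysis depends on a correlation it does not give. The absence of that correlation from an article is not itself an error. The same assumption cuts both ways, however: the printed calculation uses the raw SD of 18 and takes no credit for adjustment, so an unstated correlation cannot make its result correct.

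A reader might also infer that the plan expects a particular dropout rate. It does not. The 12 % is a switch between two methods, and dropout is listed as something to describe. Below that threshold LOCF keeps every patient in the analysis, so 53 per arm is an approximation. LOCF keeps the count but does not recover the missing information, and it may dilute the effect. What remains is that 120 is exactly 2 × 60, with no visible margin.

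Finally, the sample size sentence can be read as a within-group comparison. That reading gives 34, not 60, and conflicts with the abstract and with the planned ANCOVA, so it does not rescue the figure.

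**Conclusion.** The point holds in a limited form. On the printed inputs, an unadjusted two-arm comparison needs 63 or 64 patients per arm. The stated 60 gives 78.2 % (normal) or 77.5 % (t) with complete data, and about 72–73 % if 12 % of outcomes were missing. The arithmetic gap alone is about 2 points; the lack of a visible dropout allowance matters more, but its size depends on a rate the article does not state.

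The conclusion concerns the stated calculation, not what the trial can achieve. Baseline adjustment could bring power to 80 % or above, given r of about 0.24 with complete data, 0.41 at an assumed 12 % missing, or 0.50 at an assumed 20 %. Those correlations rest on 18 being the SD of the T2 score. If it is the SD of the change, they do not apply. This is a correctable error in a headline claim and does not threaten the trial's validity.

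**What to change.** Keep 120 patients and correct the power sentence in both the abstract and the statistical section.

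1. Name the contrast as the difference between the two groups at T2, in place of the baseline-to-T2 difference within the intervention group, and say what the SD of 18 refers to.
2. Then do one of the following:
   - state the unadjusted power, about 77–78 % with complete data and about 72–73 % if 12 % are missing; or
   - state power under the planned baseline-adjusted model, with the correlation and dropout written in and labelled as assumptions (for example r = 0.5: 88 % complete, 84 % at 12 % missing, 80 % at 20 % missing).

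The cost is a few reworded lines. The figure becomes slightly less favourable, or conditional on a stated correlation. No extra patients and no change to the analysis are needed, which suits a trial that had already recruited 80 of its 120 patients (Trial status).
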